### **Model selection by backwards selection for generalised linear and logistic mixed-effects models**

A multivariable model was first constructed using pneumococcal density (continuous data) as the response variable and including all possible covariates of interest: Group (ref: control vs LAIV), Study timepoint (ref: D0 vs D7 and D21), year of recruitment (ref:2017 vs 2018), presence of asymptomatic respiratory viruses at baseline, age in months, sex, presence of a smoker in the household, type of cooking (re:outdoor open fire vs indoor kitchen). Interactions between group and study timepoint, group and year of recruitment, as well as group and the presence of asymptomatic respiratory viruses were also included.

Backward selection was then undertaken, removing covariates to construct a new model and comparing this reduced model with the previous model using ANOVA-derived P values and Akaike information criteria (AIC). Non-informative covariates were sequentially removed in this way to arrive at the most parsimonious model for our data. Non-significant interaction terms were first removed prior to single covariates. The final model is as stated below:

Pneumococcal density ~ study timepoint + group\*year of recruitment + presence of baseline respiratory viruses + age in months + type of cooking + (1 | participant ID)

A logistic mixed-effects model with pneumococcal carriage (categorical data) as the response variable and including covariates of interest was constructed in a similar way, for each group (LAIV or control) individually. The final model is as stated below:

Presence of pneumococcal carriage ~ study timepoint + presence of baseline respiratory viruses + age in months + type of cooking + (1 | participant ID)

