**Table S2. Factors associated with pneumococcal density during the study period**

| Variable                                             | Change in log10copies/μl | Standard Error | P value # |
|------------------------------------------------------|---------------------------------|----------------|----------------------|
| LAIV receipt at Day 0 (vs control)                   | +0.339                          | 0.129          | 0.0097               |
| Asymptomatic respiratory virus at day 0              | +0.259                          | 0.097          | 0.017                |
| Day 7 ( vs day 0)                                    | +0.153                          | 0.082          | 0.081                |
| Day 21 (vs day 0)                                    | +0.272                          | 0.082          | 0.0015               |
| Recruitment in 2018 (vs 2017)                        | +0.423                          | 0.160          | 0.0091               |
| Age (in months)                                      | -0.015                          | 0.005          | 0.0030               |
| Household cooking indoors (vs outdoors) ^ | -0.275                          | 0.151          | 0.067                |
| Group:year of recruitment interaction                | -0.476                          | 0.195          | 0.016                |

#P values for factors associated with *S. pneumoniae* density are derived from a generalized linear mixed-effect model. Reference levels for each variable are given within brackets. ^Cooking inside (under a roof) compared to cooking using an indoor kitchen. Note 99% of children lived in households where wood/charcoal was primary fuel used to cook regardless of location of cooking.

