## 22 Allocation concealment, randomization and blinding procedures

### 23 Allocation concealment and randomization

Following informed consent, subjects will be assigned a unique subject identification number (section 3.2.2) and details recorded on an enrollment log. If eligibility is confirmed according to the defined inclusion and exclusion criteria (section 5.3), children will be randomized into one of the three equally sized groups as defined in section 3.1 above (for groups A, B and C).

Randomization will be undertaken using pre-prepared, sealed opaque envelopes to maintain allocation concealment. Block randomization stratified by sex will be undertaken using a computer generated randomization sequence pre-prepared by an individual not otherwise involved in the study or its analysis. The block size and randomization sequence will not be known by any member of the investigator team, hence ensuring allocation bias is avoided. Information regarding the group into which a participant has been randomized will be revealed to the team only when opening the envelope.

At the time of randomization, the person undertaking randomization will take the next envelope in numerical sequence. The randomization list will be cross-checked by a second individual both of whom will be required to sign to document the process.

The 35 subjects for group D will be recruited sequentially after recruitment in groups A, B and C have been completed, during the 2nd recruitment season (January – June 2018).

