## **128 Impact of LAIV on the nasopharyngeal microbiome**

Initial sequence data analysis will be performed as described above. Univariate and multivariate linear regression models will be used to study the effect of vaccination with LAIV on microbiota profiles at day 7 and 21 post-vaccination, adjusting for factors such as antibiotic use within the last 1 month, age and nutritional status in all multivariate analyses. Relative effect sizes and their 95% confidence intervals will be calculated for all significant OTUs. Inter-individual variability between vaccinated and unvaccinated children at day 7 and 21 will be calculated using Pearson correlations and tested for significance using the Mann-Whitney U test.

The relative and absolute abundance of the OTUs representing *S. pneumoniae* and *S. aureus* will be compared at day 7 and 21 following vaccination with baseline data and validated via qPCR. Differences in *S. pneumoniae* and *S. aureus* density at day 7 and 21 post-LAIV will be estimated using a regression model, including a fixed effect for the vaccine group and random effects for other relevant factors.

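### The final pneumococcal density model averages the LAIV–control gap over one pre-vaccination and two post-vaccination visits, so its LAIV receipt coefficient does not estimate the effect at day 7 or day 21

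*Combined protocol and SAP*

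**What the plan says.** The appendix section on model selection describes a starting model for density in which visit is a three-level factor, "Study timepoint (ref: D0 vs D7 and D21", so the baseline swab is a response row and not a covariate. On the starting interactions it says: "Interactions between group and study timepoint, group and year of recruitment, as well as group and the presence of asymptomatic respiratory viruses were also included". Terms were then dropped by comparing nested models on ANOVA P values and AIC, interactions first ("Non-significant interaction terms were first removed prior to single covariates"). The final formula begins "Pneumococcal density ~ study timepoint + group\*year of recruitment + presence of baseline respiratory viruses", followed by age, type of cooking and a random intercept per child. It contains no group by timepoint term.

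Table S2 reports the group term from this model as "LAIV receipt at Day 0 (vs control) | +0.339 | 0.129 | 0.0097". Tables S4 (2017) and S5 (2018) use the same row label.

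Protocol section 128 had planned something different: density differences at days 7 and 21 after LAIV, from a regression "including a fixed effect for the vaccine group and random effects for other relevant factors". It also says that abundance at those days will be compared with baseline. Randomisation was stratified by sex (section 23: "Block randomization stratified by sex will be undertaken").

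**The concern.** A model with day 0 in the outcome and no group by timepoint term forces the two arms to differ by the same amount before vaccination as after it. Change from baseline is then identical in both arms by construction. What remains is a group gap averaged over visits, one of which the vaccine cannot have affected. Readers will take a row labelled as LAIV receipt to be the effect of the vaccine on density.

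Primary objective (iii) asks whether LAIV alters the pneumococcal burden, and section 123 cites 1.5- to 2-fold increases as possibly relevant to transmission. If the coefficient is read as the effect, both its size and its attribution are uncertain. The first is diluted by the baseline visit; the second is mixed with whatever difference existed at baseline.

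**Working it through.** **1. Reproducing the printed figures.** The coefficients cannot be refitted without patient data, but they can be checked.
- S2: 0.339/0.129 = 2.63, giving P = 0.0086 (normal) or 0.0090 (t, about 313 df). The table prints 0.0097, which is close but not exact.
- S4: 0.323/0.127 = 2.54 on 168 df gives P = 0.0119; the table prints 0.012.
- S2 retains group by year with 2017 as reference, so +0.339 is the 2017 gap only. The implied 2018 gap is 0.339 − 0.476 = −0.137; S5 prints −0.139.

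**2. Is day 0 in the outcome?** S4 prints 168 between-child and 345 within-child df. With 5 between-child parameters (intercept, group, virus, age, cooking) there are about 168 + 5 = 173 children. Three visits each give 2 × 173 − 2 = 344 within-child df; days 7 and 21 alone would give about 172. The three-visit reading fits.

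**3. What the coefficient is.** Let b0 be the LAIV–control gap at day 0, and d7 and d21 the between-arm differences in change from day 0. With complete data and a random intercept, the group coefficient is the mean of the three visit gaps:

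[b0 + (b0 + d7) + (b0 + d21)]/3 = b0 + (d7 + d21)/3.

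**4. Dilution when b0 = 0 and the effect d is constant.** The coefficient is 2d/3.
- 2-fold: 0.301 × 2/3 = 0.201, or 1.59-fold.
- 1.5-fold: 0.176 × 2/3 = 0.117, or 1.31-fold.
- Read this way, +0.339 would correspond to 0.339 × 3/2 = 0.51, that is 3.2-fold and not 2.2-fold.

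**5. How much of a chance day 0 gap passes through.** From S4, with 2:1 arms (115 and 58, assumed):
- Within-child variance: 0.112² × 173/2 = 1.085.
- Between-child variance: about 0.26, from the group SE of 0.127.
- Within-child correlation ρ: 0.26/(0.26 + 1.085) ≈ 0.19. The same method gives about 0.32 for S5.
- A chance gap is expected to reach the coefficient at (1 + 2ρ)/3, which is 0.46 to 0.55.
- The SD of a chance day 0 gap in 2017 is √[1.345 × (1/115 + 1/58)] ≈ 0.19 log10.

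**6. Can the tables separate the two explanations for 2017?** S4's changes for both arms together are +0.025 and −0.065, mean −0.020. Let c be the mean control change and d the mean difference in change. With 2:1 arms, −0.020 = c + 2d/3 and 0.323 = b0 + 2d/3, so b0 = 0.343 + c.
- If controls were flat (c = 0), b0 ≈ 0.34 and d ≈ −0.03: the whole gap predates vaccination.
- If b0 = 0, controls fell by about 0.34 and d ≈ +0.48.

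Both are compatible with Table S3, whose mean control change over both years is (0.022 + 0.232)/2 = 0.127. With 58 and 50 controls (assumed), the 2018 control change would be about 0.27 in the first case and 0.67 in the second.

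**7. The dropped contrast, approximated over both years.** Arm sizes of 213 and 108 come from Table S10 and are assumed to apply here.
- Day 7: LAIV change (0.153 × 321 − 0.022 × 108)/213 = 0.219; difference from control 0.219 − 0.022 = +0.20.
- Day 21: LAIV change (0.272 × 321 − 0.232 × 108)/213 = 0.292; difference 0.292 − 0.232 = +0.06.
- SE about 0.174, so the 95% CIs are −0.14 to 0.54 and −0.28 to 0.40.

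**8. Does non-significance justify the drop?** The same variances and arm sizes, ignoring year, give:
- 2-df group by timepoint test: power about 42% for a 2-fold and 17% for a 1.5-fold effect.
- Three-visit group term: SE 0.093, about 58% for 2-fold.
- Mean of days 7 and 21 adjusted for day 0: SE 0.102 but an undiluted effect, about 84% for 2-fold.

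The last two imply an effective sample size ratio of (0.301/0.102)² / (0.201/0.093)² ≈ 1.9. With ρ = 0.32 it is about 2.2.

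**The case against.** The best defence is that allocation was randomised. With no vaccine effect the group term has expectation zero, and its standard error already allows for chance day 0 differences. With a constant post-vaccination effect it recovers two thirds of that effect, so it errs towards caution. All of that stands. It supports the term as a diluted test of whether LAIV did anything, but not as an estimate of the effect at either visit. Nor is group by timepoint the only informative term: a group effect fitted to days 7 and 21 alone would serve, which is why the repair can use one.

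Second, Tables S2 to S5 sit in a supplementary appendix and are titled as factors associated with density. Nothing in the supplied text calls S2 the primary or headline result, and the main report, which is not supplied, may give arm-specific comparisons. This stands and limits the point to the model and tables as printed.

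Third, section 128 aims at days 7 and 21, so the plan does not put day 0 in the outcome. This is correct. Its regression names neither baseline adjustment nor group by time, but that is a gap in specification and a milder matter.

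Fourth, other omissions from the final model matter little here. S4 and S5 are fitted by year, so their time courses differ freely (day 21 change −0.065 against +0.685; z = 0.750/√(0.112² + 0.116²) ≈ 4.65). Yet the group estimates hardly move: 0.339 to 0.323, and −0.137 to −0.139. Leaving out sex, a balanced stratifier, costs some precision and does not bias the contrast.

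**Conclusion.** The *LAIV receipt* rows in S2 (2017 only), S4 and S5 are year-specific group differences averaged over three visits, one before vaccination. They do not estimate the post-vaccination effect that section 128 set out to measure. Under balance at day 0 the understatement is one third on the log scale. Selection on significance is weak ground for the missing interaction, given about 42% power at a 2-fold effect.

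A reader might go further and infer that the 2017 result is a baseline imbalance reported as a vaccine effect. The documents do not show that: no day 0 density by arm is in the supplied text, the figure of the distributions is not visible, and a balanced baseline with an effect of about +0.48 fits as well as a gap of about 0.34 with none. A reader might also infer that the coefficient has nothing to do with the vaccine; randomisation rules that out in expectation. Nor does 2018 show a reversal of the effect: −0.139 with SE 0.155 (P = 0.37) is compatible with no difference.

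The figures assume complete data, equal variances and correlations across visits, 2:1 allocation within year, and the Table S10 arm sizes. The averaging itself follows from the printed formula and needs none of the variance figures.

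**What to change.** For objective (iii), replace the selected model with a fixed one:
- Outcome: log10 density at days 7 and 21, with day 0 density as a covariate. A longitudinal model constrained to equal day 0 means is an alternative.
- Terms: group, time, group by time, year, sex, age, and the adjusters section 128 already names (recent antibiotic use and nutritional status), with a random intercept per child. Keep the group terms regardless of P value or AIC.
- State how non-carriers enter log10 density; section 123 considers carriage of only 80% to 90%.
- Report the LAIV–control difference with 95% CI at day 7 and at day 21, and day 0 density by arm and year.
- Relabel the group rows of S2, S4 and S5 as year-specific differences averaged over three visits including the pre-vaccination one.
- Time by year may be added as a sensitivity analysis.

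The cost is revised analysis text and a re-run on data already collected, with no new samples or children. For a sustained effect of the same size the baseline-adjusted analysis is more precise, but the P value may turn out less favourable than the one printed.

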**Table S1. Factors associated with pneumococcal prevalence in the Control group**

| Variable                                             | Odds ratio | 95% CI      | P value # |
|------------------------------------------------------|------------|-------------|----------------------|
| Asymptomatic respiratory virus at day 0              | 0.92       | 0.38 – 2.24 | 0.86                 |
| Day 7 (vs day 0)                                     | 1.16       | 0.55 – 2.44 | 0.70                 |
| Day 21 (vs day 0)                                    | 1.35       | 0.63 – 2.88 | 0.44                 |
| Age (in months)                                      | 0.99       | 0.94 – 1.04 | 0.64                 |
| Household cooking indoors (vs outdoors) ^ | 0.65       | 0.16 – 2.71 | 0.55                 |

#P values for factors associated with *S. pneumoniae* prevalence are derived from a generalized logistic mixed-effect model. CI = confidence interval. Reference levels for each variable are given within brackets. ^Cooking inside (under a roof) compared to cooking using an indoor kitchen. Note 99% of children lived in households where wood/charcoal was primary fuel used to cook regardless of location of cooking.

**Table S2. Factors associated with pneumococcal density during the study period**

| Variable                                             | Change in log10copies/μl | Standard Error | P value # |
|------------------------------------------------------|---------------------------------|----------------|----------------------|
| LAIV receipt at Day 0 (vs control)                   | +0.339                          | 0.129          | 0.0097               |
| Asymptomatic respiratory virus at day 0              | +0.259                          | 0.097          | 0.017                |
| Day 7 ( vs day 0)                                    | +0.153                          | 0.082          | 0.081                |
| Day 21 (vs day 0)                                    | +0.272                          | 0.082          | 0.0015               |
| Recruitment in 2018 (vs 2017)                        | +0.423                          | 0.160          | 0.0091               |
| Age (in months)                                      | -0.015                          | 0.005          | 0.0030               |
| Household cooking indoors (vs outdoors) ^ | -0.275                          | 0.151          | 0.067                |
| Group:year of recruitment interaction                | -0.476                          | 0.195          | 0.016                |

#P values for factors associated with *S. pneumoniae* density are derived from a generalized linear mixed-effect model. Reference levels for each variable are given within brackets. ^Cooking inside (under a roof) compared to cooking using an indoor kitchen. Note 99% of children lived in households where wood/charcoal was primary fuel used to cook regardless of location of cooking.

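### The LAIV row of Table S2 (+0.339, P=0.0097) is the effect in 2017 recruits only but is not labelled so; no effect over both years is reported, and an approximate average is +0.137 log10 (P=0.16)

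*Combined protocol and SAP*

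**What the plan says.** Burden of *S. pneumoniae* is part of the third primary objective, and its density by quantitative PCR is a primary endpoint. For density, protocol section 128 (Impact of LAIV on the nasopharyngeal microbiome) plans that day-7 and day-21 differences be "estimated using a regression model, including a fixed effect for the vaccine group and random effects for other relevant factors". It names no group-by-year interaction.

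The appendix section on model selection describes a different route. The starting model held eight covariates, among them "year of recruitment (ref:2017 vs 2018", and three interactions: group with timepoint, group with year, and group with baseline virus. Covariates were removed by "comparing this reduced model with the previous model using ANOVA-derived P values and Akaike information criteria (AIC". On the interactions it says: "Non-significant interaction terms were first removed prior to single covariates". The final model begins "Pneumococcal density ~ study timepoint + group\*year of recruitment + presence of baseline respiratory viruses" and continues with age, cooking type and a participant random effect. Group-by-year stayed; group-by-timepoint did not.

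Table S2 reports that model. Its row "LAIV receipt at Day 0 (vs control" is +0.339 (SE 0.129, P=0.0097), and its row "Group:year of recruitment interaction" is −0.476 (SE 0.195, P=0.016). Neither the LAIV row nor the footnote ties +0.339 to a year. Tables S4 and S5 give separate models for 2017 (LAIV +0.323, SE 0.127, P=0.012) and 2018 (−0.139, SE 0.155, P=0.37).

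**The concern.** When a two-level factor is interacted with another factor under reference coding, its main-effect row is the effect at the reference level, not an average. Read as labelled, Table S2 says that LAIV recipients had 2.18-fold higher density (10^0.339) over the study, with P below 0.01. The model says this of 2017 recruits only; for 2018 the point estimate has the opposite sign.

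The size matters on the protocol's own scale. Section 123 says that 1.5- to 2-fold increases in carriage density may be relevant to transmission. A 2.18-fold effect lies above that range and a 1.37-fold effect below it.

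Two features of the model add to the problem. The interaction that turns the LAIV row into a single-season effect was kept because of the data, so the P values attached to it and to the row take no account of the search. And without a group-by-timepoint term, the LAIV coefficient is a group difference taken over all three visits, including day 0, when no child had yet been vaccinated.

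**Working it through.** **1. Reproduce the printed row.** 0.339 / 0.129 = 2.63, two-sided P = 0.0086 (normal) or 0.0094 (t, 168 df, the df printed for the LAIV row in Table S4). Rounding of the coefficient and SE takes the latter to 0.0098, so the printed 0.0097 is consistent.

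**2. Year-specific effects from Table S2.**
- 2017 (reference) = main effect = +0.339. Table S4: +0.323.
- 2018 = main effect + interaction = 0.339 − 0.476 = −0.137. Table S5: −0.139.

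The separate fits agree with the joint model to within 0.02, which confirms that the row is a 2017 effect.

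**3. Average over the two years.** Inverse-variance pooling of Tables S4 and S5:
- weights: 1/0.127² = 62.0 and 1/0.155² = 41.6, or 0.598 and 0.402;
- estimate: 0.598 × 0.323 − 0.402 × 0.139 = +0.137;
- SE: (62.0 + 41.6)^−0.5 = 0.098;
- 95% CI −0.055 to +0.330; z = 1.40; P = 0.16.

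As ratios: 1.37-fold, CI 10^−0.055 = 0.88 to 10^0.330 = 2.14.

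**4. Other weights.** With weight w on 2017, the estimate is w·b₁ + (1−w)·b₂, with variance w²·SE₁² + (1−w)²·SE₂². The Table S2 version needs a covariance that is not printed. I assumed it equals minus the variance of the main effect, which gives a 2018 SE of √(0.195² − 0.129²) = 0.146 (Table S5: 0.155).

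| Weight on 2017 | From S4 and S5 | From S2 |
|---|---|---|
| Equal, 0.50 | +0.092, P=0.36 | +0.101, P=0.30 |
| Control-arm split in Table S7, 48/90 | +0.107, P=0.28 | +0.117, P=0.23 |
| Planned season targets, 195/330 | +0.134, P=0.17 | +0.144, P=0.14 |
| Inverse variance | +0.137, P=0.16 | +0.131, P=0.18 |

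Setting the same formula to z = 1.96, 2017 would need about 73% of the weight (S4 and S5) or 70% (S2). The planned share is 195/330 = 59%.

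**5. The interaction and the selection.** From Tables S4 and S5: −0.139 − 0.323 = −0.462, SE √(0.127² + 0.155²) = 0.200, P = 0.021. Table S2 prints P=0.016. Multiplying by the three candidate interactions gives 3 × 0.016 = 0.048 or 3 × 0.021 = 0.063. This is a rough allowance only; the effect of the whole backward search cannot be computed from the documents.

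**6. Day 0.** Under a random-intercept model with all three visits present, the group coefficient is the mean of the day-0, day-7 and day-21 group differences. If the groups did not differ at day 0, it is two thirds of the mean post-vaccination difference. If they differed by chance, it carries a third of that imbalance. The appendix text does not give the day-0 difference, so neither the direction nor the size is known.

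**The case against.** Several points on the other side stand.

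- **The information is largely printed.** The interaction row, the 2017 reference year and both year-specific tables are there, and a careful reader can recover the meaning. A reader might infer concealment; the documents do not support that. The fault is a missing label and a missing overall estimate.
- **Nothing shows that +0.339 was the trial's stated answer.** Table S2 is a supplementary table of associated factors, and the main report is not among the documents.
- **A season interaction is not arbitrary.** Protocol section 27 allows the vaccine strains to change for 2017-18, and effects of opposite sign may mean that an average describes neither season. This is a reason to keep both years visible, not to leave the 2017 row unlabelled.
- **The average does not show that LAIV has no effect.** Its CI includes the 1.5- to 2-fold range, and it shares the day-0 defect.

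Two further stronger readings are tempting. The first is that selection displaced a promised adjustment set. The sentence "adjusting for factors such as antibiotic use within the last 1 month, age and nutritional status in all multivariate analyses" concerns models of microbiota profiles and lists examples; the density analysis is in a separate paragraph that names no covariates. The second is that the omitted timepoint-by-year term distorts the LAIV effect, since the day-21 change is −0.065 in 2017 and +0.685 in 2018. Tables S4 and S5 are fitted by year and so already allow for it, and their LAIV effects hardly differ from those of Table S2.

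**Conclusion.** The point holds as a fault of labelling, reporting and model choice on a primary endpoint. The +0.339 (P=0.0097) is a single-season estimate. Over both seasons the appendix's own figures give about +0.14 log10, or +0.09 to +0.14 depending on the weights, with P from 0.14 to 0.36. An overall increase in density is therefore not shown; it is also not ruled out.

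This rests on treating the two yearly fits as independent, on normal approximations, on the assumed covariance where Table S2 is used, and on weights that stand in for actual recruitment by year, which the documents do not give for both arms together. The +0.137 is approximate for a further reason: like Tables S2, S4 and S5, it is not a purely post-vaccination contrast. The year interaction is borderline once three candidates are allowed for (about 0.05 to 0.06) and should be read as exploratory.

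**What to change.** 1. Relabel the row in Table S2 as LAIV v control, 2017 recruits only, and print the 2018 effect (−0.137) with its SE beside it.
2. Report the year-averaged LAIV-control contrast, with its CI and a named weighting (for example, each season's share of randomised children), as the whole-trial estimate. Show the year-specific effects and the interaction P below it as exploratory.
3. Replace backward selection by one fixed model of day-7 and day-21 density: group-by-visit, day-0 density as covariate, sex (the randomisation stratifier), season and age. Add group-by-season only for the exploratory year effects.
4. If the selected model is kept as supplementary, state that its P values take no account of selection and that its LAIV coefficient includes day 0.

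The cost is one refit, relabelled tables and a paragraph of text. The overall figure will probably be less favourable than +0.339. With year effects of opposite sign the average is only a summary, so both years must stay visible.
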